#### Sample size calculations

Sample size calculations are based on the recent meta-analysis (N = 2820) by Malström et al. [35] who looked at the recurrence after standard treatment (instillations of mitomycine or BCG). This is the group that corresponds best with our placebo-group (standard care). The absolute difference between the placebo- and the Selenium-group is based on the difference in percent of recurrence after five years (average of time after randomization in our study). A difference of 12,5% in absolute reduction can be expected, considering that the intake of 200 μg of SelenoPrecise yeast increases the plasma selenium by ± 100 ng/mL [29] and that, according to epidemiological studies, the incidence of bladder cancer decreases by 25% if the plasma selenium increases by 10 ng/mL [10].

To detect an absolute decrease of 12,5% in the recurrence-free rate by selenium versus placebo, 700 patients are needed, taking into account a drop out of 25% with a power of 86% (two-sided test).

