## Methods

### Clinical design

SELEBLAT is a phase III randomized, double-blind, placebo-controlled, multicentre, academic trial with 200 μg/day Selenium-yeast supplementation during 3 years with a subsequent follow-up period of 3 years aimed at the prevention of recurrence of non-muscle-invasive bladder cancer (NMIBC). SELEBLAT was initiated by the Department of General Practice of the University of Leuven and the Department of Urology of the University hospitals of Leuven, Belgium with funding by the Agency for Innovation by Science and Technology Belgium (IWT).

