#### Participant follow-up

Study participants are supplied with the study drug and followed on a bi-annual basis for a period of up to three years. This follow-up phase entails questionnaire distribution and monitoring for adverse events. Study questionnaires capture the onset of new illnesses and symptoms, including potential selenium-related toxicities.

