The SELEBLAT study is well-designed. Selenium-yeast is a safe and cheap medicine. A computerized program performs our randomization. Neither the investigators, nor the research nurses have access to the randomization numbers. All study personnel is blinded for the medication. Both treatment groups are regularly compared on similarity of prognostic characteristics such as age, gender, smoking, grade of tumour, baseline selenium level and co-morbidity. We will report reasons and numbers of those patients lost to follow up. Both an intention to treat and a per protocol analysis will be performed. For hypothesis building subgroup analyses and analyses of interactions will be performed, as we have demographic and clinical data and questionnaires results on diet and Quality of Life. Standard treatment will be compared between the intervention and the placebo group. Additional intake of selenium by food supplements will be analyzed and compliance will be reported. Our primary outcome measures are both clinical and histologically confirmed recurrences as frequently patients with clinical recurrence are only cauterized without taking a biopsy. Cauterization only reduces the risk of perforation of the bladder. All subsequent patients undergoing TUR operation are included meeting the inclusion criteria. We decided to include both primary and second primary tumours, because the incidence of bladder cancer is low, while the prevalence and the rate of tumour recurrence is high [24]. Recurrence within the first three months after TUR is considered as residual untreated disease. Although bladder cancer and prostate cancer occur together in 10% of the cases [59,60], we decided to exclude patients with prostate cancer too. We deliberately did not exclude any patient for presence of co-morbidity or age aiming for a study population, which represents as far as possible the normal population diagnosed with bladder cancer. We intend to reach the calculated sample size by pooling of our results with the results from the Selenib study (UK), which is similar in design. Progress of the study can be followed on the website: http://www.genepid.bham.ac.uk/Seleblat_Recruitment.shtml. The first results of our study can be expected for 2014.

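### The 12.5-point design effect does not follow from the selenium figures given for it, its sign is reversed, and the 86% power and five-year horizon rest on a control rate and follow-up that the protocol does not fix

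*Protocol article*

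**What the plan says.** All from the protocol article.

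- **Target and size** (Sample size calculations): "To detect an absolute decrease of 12,5% in the recurrence-free rate by selenium versus placebo, 700 patients are needed". The allowance for loss and the power come at the end of that sentence: "taking into account a drop out of 25% with a power of 86% (two-sided test"). Neither the placebo recurrence rate nor alpha is given. The placebo rate is left to a cited meta-analysis.
- **Basis for the effect** (same section): the tablets raise plasma selenium by about 100 ng/mL, and "the incidence of bladder cancer decreases by 25% if the plasma selenium increases by 10 ng/mL".
- **Time horizon** (same section): the difference is "based on the difference in percent of recurrence after five years (average of time after randomization in our study").
- **Follow-up elsewhere**: Clinical design gives three years of supplementation "with a subsequent follow-up period of 3 years". Participant follow-up says patients are "followed on a bi-annual basis for a period of up to three years". Participant recruitment runs from September 2009 to August 2012. The Discussion says: "The first results of our study can be expected for 2014".
- **Primary test** (Statistical analysis): log-rank.

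**The concern.** This one section sets the target effect, the sample size and the time horizon. The Discussion keeps the calculated size as the goal, to be reached by pooling with a second trial, so the calculation still governs what the trial can claim.

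Four things in it do not fit together. The effect is offered as a derived quantity, but the stated premises give something very different. The target sentence describes harm. The power depends on a control rate that the reader cannot see, and the rate that the text hints at does not return 86%. The five-year horizon matches neither the three-year follow-up statement nor the 2014 date. An assumption would therefore pass as evidence, and a main analysis run too early would have clearly less power than stated.

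**Working it through.** **Inputs.** From the article: 700 patients, 25% drop-out, 12.5 points, 86% power, two-sided test, log-rank. Assumed because not stated: alpha 0.05, 1:1 allocation, and the control rate (varied below). Evaluable after a 25% loss: 700 × 0.75 = 525, or 262.5 per arm.

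**1. Effect size.** A rise of 100 ng/mL is ten steps of 10 ng/mL.

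- Adding the steps gives 10 × 25% = 250%, which is impossible.
- Compounding gives 1 − 0.75^10 = 1 − 0.056 = 94.4% relative reduction. That is 38, 47 or 57 points at control rates of 40%, 50% or 60%.
- One step at 50% control gives 0.25 × 50 = 12.5 points, exactly the stated figure.
- For ten steps to give 12.5 points, the control rate would have to be 12.5 / 0.944 = 13.2%. That cannot be the design case: with 262.5 per arm, power for 12.5 points is already 98.7% at a 20% control rate and is higher still below that.

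**2. Can 86% be reproduced?** Two proportions, pooled variance under the null, n = 262.5, p̄ the mean of the two rates:

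power = Φ{ [0.125 − 1.960 √(2p̄(1−p̄)/n)] / √([pc(1−pc) + pt(1−pt)]/n) }

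- 40% v 27.5%: (0.125 − 0.0809) / 0.0409 = 1.078, power **85.95%**. The stated figure is reproduced.
- 50% v 37.5%: (0.125 − 0.0849) / 0.0430 = 0.934, power **82.5%**.

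Log-rank (Schoenfeld), with HR = ln(1−pt)/ln(1−pc), D the expected number of recurrences, and power = Φ(|ln HR| √D / 2 − 1.960):

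- 40% v 27.5%: HR 0.63, D = 262.5 × 0.675 = 177, power **86.9%**.
- 50% v 37.5%: HR = ln 0.625 / ln 0.5 = 0.678, D = 262.5 × 0.875 = 229.7, power Φ(2.944 − 1.960) = **83.7%**.

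**3. Where 700 could come from at 50%.** Recurrences needed for 86% power: 4(1.960 + 1.080)² / (ln 0.678)² = 245. Patients: 245 / 0.4375 = 560. Then 560 × 1.25 = 700, whereas allowing for a true 25% loss gives 560 / 0.75 = 747. Other inputs also return 700: 45% v 32.5% by two proportions needs 560, and again 560 × 1.25 = 700. At 40% v 27.5%, 526 / 0.75 = 702 with no error in the allowance.

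**4. Follow-up in 2014.** The midpoint of entry is about March 2011. Mean follow-up is 2.8 years at the start of 2014, 3.3 at mid-year and 3.8 at the end. The longest possible is about 5.3 years. A mean of five years is reached about March 2016.

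Log-rank power with 525 evaluable, constant hazards set by the five-year rates, and uniform entry over three years:

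| Control rate | Five years each | Cut at mid-2014 | Cut at end-2014 | Six years each |
|---|---|---|---|---|
| 40% | 87% | 74% | 79% | 91% |
| 50% | 84% | 71% | 75% | 88% |
| 60% | 84% | 72% | 76% | 88% |
| 70% | 88% | 78% | 82% | 91% |

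**5. Direction.** The objective in the Introduction is to reduce recurrence. A benefit of 12.5 points is an increase in the recurrence-free rate.

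**The case against.** **A reader might infer that the 86% is wrong and that true power is 82–84%.** The document does not support that. The control rate is not given, and 40% v 27.5% reproduces 700 and 86% with the drop-out handled correctly. The ×1.25 explanation is one of several that fit. The hint towards 50% (25% of 50 is 12.5) is circumstantial, so the 82–84% holds only if 50% was used. By log-rank the worst case near 55% control is about 83.5%, so even then the shortfall is small.

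**A reader might infer that the trial will be analysed in 2014 with 71–82% power.** The Discussion speaks only of first results, and the Statistical analysis section gives the final analysis no date. The three-year statement under Participant follow-up concerns drug supply, questionnaires and adverse events, and may describe only the treatment phase. Six years per patient, as Clinical design implies, would give 88–91%. This objection stands: the low figures are conditional on a cut-off that the article does not state.

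**The justification of the effect does not alter the power to detect 12.5 points, and compounding over ten steps is an extrapolation.** Both are true. But the article itself joins the 100 ng/mL rise to the 25% per 10 ng/mL and says that 12.5 points can be expected from them, and neither adding nor compounding gives that.

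**The reversed sign is a slip of wording.** Probably so, since the preceding sentences speak of a reduction in recurrence. It still sits in the sentence that defines the target.

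**Conclusion.** The point holds as a fault in the basis of the design effect, with a power and a horizon that the article leaves open.

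- **Established from the text alone:** the plasma figures do not yield 12.5 points (94% relative reduction if compounded). The target sentence is reversed. A five-year average is not available in 2014 (2.8 to 3.8 years) and does not agree with follow-up of up to three years.
- **Conditional on 50% control, alpha 0.05 and 1:1 allocation:** power is 82.5% to 83.7% against 86%, and a true 25% allowance on 560 evaluable gives 747 rather than 700.
- **Conditional on the main analysis being cut in 2014, with constant hazards and uniform entry:** log-rank power is about 71–82% for control rates of 40–70%.

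It is not shown that 86% is miscalculated.

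**What to change.** In Sample size calculations:

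1. Call 12.5 points an assumed absolute **increase** in the five-year recurrence-free rate, and stop presenting it as a result of the plasma figures.
2. State the control rate and alpha used, and the power for 700 patients after a true 25% loss. If 50% was used, that is about 82–84%. If 40% was used, 86% can stand.
3. Tie the final analysis to the number of recurrences that the stated power needs: about 245 (HR 0.68) for 86% at 50% v 37.5%, or about 173 (HR 0.63) at 40% v 27.5%. Treat 2014 as first results only.

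Reconcile the follow-up length across Clinical design, Participant follow-up, Sample size calculations and the Discussion.

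Cost: changes of wording and one recalculation. The stated power may fall by 2 to 4 points (86 − 83.7 = 2.3; 86 − 82.5 = 3.5), and the final report may come later than 2014.

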#### Interim analyses

An independent data and safety monitoring board will periodically review the efficacy and safety data. Two formal interim analyses of efficacy will be performed as soon as the first 100 patients have reached one and two years after randomization. The interim analyses will enable the study to be stopped early if a clear result should emerge. This will take place if a statistically significant increase or decrease in recurrence rate of at least 10% has been found.

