#### Participant recruitment

Patients are recruited by the participating urologists of 15 hospitals throughout Belgium (Flanders and Brussels) from September 2009 to August 2012. All subjects have to master the Dutch or French language and may be excluded due to illness, mental sickness or incapacity to comprehend the questions as evaluated by the treating clinician. Eligible patients receive oral and written information (information brochure) from the research nurse and sign an informed consent form. The procedures followed are in accordance with the ethical standards of the responsible committee on human experimentation (institutional and national) and with the Helsinki Declaration of 1975, as revised in 2008. The study has been approved by the ethical review board of the University Hospital of Leuven acting as the central ethical review board, by the trial steering committee and by the appropriate ethical review boards related to the hospitals in which it is performed. A Data Safety Monitoring Board (DSMB), comprised of individuals with expertise in the areas of medicine and biostatistics, has been established to serve as an external review committee to monitor the progress of the study including accrual and adverse events.

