#### Randomization

Randomization is stratified by treatment centre. Once a patient is deemed to be eligible for the trial and has given written consent, a trained research nurse randomizes the patient by using the database. A computerized algorithm randomly assigns the patients to a treatment arm. All study personnel and participants are blinded to treatment assignment for the duration of the study. To evaluate patient blinding, patients are asked by a questionnaire to evaluate which treatment they believe they have received (selenium, placebo, or don't know). If patients answer either selenium or placebo, they are asked to indicate what led to that belief.

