#### Statistical analysis

Final statistical analysis is on an intention-to-treat basis. Kaplan-Meier estimates of a recurrence-free interval are used to compare treatment groups descriptively, whilst log-rank tests are used to test the hypothesis of no difference between treatments. Cox proportional hazards regression models are used to estimate the Hazard risks and 95% confidence intervals comparing patients randomized to active selenium versus placebo with and without adjustment for age, sex and stage at time of diagnosis. A per protocol analysis will be performed as a sensitivity analysis. We will also test for interactions with possible additional effect modifiers such as smoking, selenium at baseline as an indicator of selenium intake. For secondary outcome measures, treatment arms are compared in terms of progression-free interval using Kaplan-Meier and log-rank tests. The reasons for excluding patients from the analysis are clearly reported.

All analyzes are performed using STATA (StataCorp. 2009. *Stata Statistical Software: Release 11*. College Station, TX: StataCorp LP)

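### The interim efficacy rule stops the trial on bare statistical significance with no interim boundary; with 0.05 at every look, overall two-sided type I error would be about 12–13% on the first 100 patients

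*Protocol article*

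**What the plan says.** The Interim analyses section of the protocol article fixes the number and timing of the looks: "Two formal interim analyses of efficacy will be performed as soon as the first 100 patients have reached one and two years after randomization". It then gives the criterion for stopping early: "This will take place if a statistically significant increase or decrease in recurrence rate of at least 10% has been found". It names no nominal level, boundary or alpha spending, and no level reserved for the final test. It does not say whether 10% is absolute or relative, at what time it is measured, or which patients enter the look.

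Other sections bear on this only indirectly:

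- Statistical analysis plans an ordinary log-rank test and "Hazard risks and 95% confidence intervals".
- Sample size calculations gives the target, "To detect an absolute decrease of 12,5% in the recurrence-free rate by selenium versus placebo, 700 patients are needed", and continues: "taking into account a drop out of 25% with a power of 86% (two-sided test". The interim looks are not mentioned there.
- No section states a value for alpha.

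**The concern.** Repeated testing at an ordinary significance level gives chance several opportunities to end the trial or to produce a positive final result. Here the section gives an actual decision criterion, so this is more than a detail left open for another document. The only inferential threshold in the criterion is significance, in either direction, at looks triggered by 100 of 700 planned patients. Applied as written at a conventional level, the rule could end a phase III trial on few recurrences and a chance difference, and an effect estimated at such a stop would tend to be exaggerated. If no adjustment was intended, the trial's overall error rate is well above the level a reader would assume. If one was intended, the published criterion does not show it, and two boards could apply the rule differently to the same data.

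**Working it through.** **1. The plan's own figure.** The placebo recurrence rate is not stated, so 700 cannot be reproduced from stated inputs alone. Assume 1:1 allocation, two-sided 0.05, and 40% v 27.5% recurrence:

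n per arm = [1.96·√(2·0.3375·0.6625) + 1.080·√(0.40·0.60 + 0.275·0.725)]² / 0.125² = (1.311 + 0.716)² / 0.015625 ≈ 263.

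That is 526 evaluable patients, and 526/0.75 ≈ 702. With 525 evaluable, power is 85.9%. At 50% v 37.5% the need would be 774. A single fixed test at 0.05 is therefore enough to explain 700; nothing in the figure points to an interim adjustment.

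**2. Three tests at 0.05, looks on the first 100 patients.** Under no effect the three log-rank statistics are approximately trivariate normal with correlation √(D_i/D_j), where D is the number of recurrences. Take, as an assumption, 20 and 35 recurrences at the looks and 525 × 0.5 = 262.5 at the end. The correlations are:

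- look 1 with look 2: √(20/35) = 0.76
- look 2 with final: √(35/262.5) = 0.37
- look 1 with final: √(20/262.5) = 0.28

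The chance of |Z| > 1.96 at least once is 12.2%, of which 8.0% arises at the two interim looks.

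| Recurrences at look 1 / look 2 / final (assumed) | Interims alone | Overall |
|---|---|---|
| 10 / 20 / 262.5 | 8.3% | 12.7% |
| 20 / 35 / 262.5 | 8.0% | 12.2% |
| 20 / 35 / 350 | 8.1% | 12.3% |
| 30 / 45 / 288.75 | 7.7% | 11.9% |

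Simulated log-rank trials gave 12.0–13.2%. For orientation, three independent tests would give 1 − 0.95³ = 14.3%, and three equally spaced looks 10.7%. The final size matters little, which is useful because the Discussion expects to reach 700 only by pooling with another trial.

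**3. Does the 10% condition help in 100 patients?** For a crude comparison of 50 v 50, the smallest significant difference is 1.96·√(2p(1−p)/50): 14 points at p = 15%, 16 at 20% and 18 at 30%. It drops to 10 points only when p is about 7% (1.96·√(2·0.07·0.93/50) = 0.100). Unless recurrence at the look is very low, an absolute 10-point condition removes few false stops.

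**4. If everyone randomised by the look is analysed.** Without a binding 10% condition, overall error is about 12–13% (one set of simulated trials gave 11.4–12.6%). With 10% read as an absolute difference the condition does bind:

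- at about 100 patients per year, the first-year accrual in Baseline characteristics: roughly 7–11%
- at 700/3 ≈ 233 per year, the pace needed to recruit 700 "from September 2009 to August 2012": roughly 5–8%

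These filtered figures depend on the assumed recurrence rate and on how the 10 points are measured (crude proportions, or Kaplan–Meier estimates at a fixed time). They are orders of magnitude.

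**5. After a fix.** With 20, 35 and 262.5 recurrences, p<0.001 at each interim and 0.05 at the end gives about 5.2%; a final level of about 0.048 brings it back to 5%. A constant level at all three looks would have to be about 0.019–0.020.

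**The case against.** The strongest reply is that a journal article condenses the full protocol, and a boundary may sit in a monitoring-board charter or analysis plan that is not shown. That stands as far as it goes: the article does not say that each look uses 0.05, nor that the looks are unadjusted. A reader might infer that the trial has a type I error of 12.5%; the text supports this only conditionally. What survives is that the published stopping criterion is significance plus 10%, with nothing to show that significance means anything other than the ordinary level.

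Other tempting inferences go further than the text:

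- **That both looks use only the first 100 patients and ignore the rest.** The wording sets the trigger for the look. The analysis set is not defined, and more than 100 patients would be randomised by then.
- **That the 10% condition gives no protection.** This is nearly so for 50 per arm, but not if all randomised patients are analysed and 10% is absolute.
- **That 10% is too lenient because it is below the planned 12.5 points.** The 12.5 points refer to the "difference in percent of recurrence after five years (average of time after randomization in our study", whereas the looks are triggered at one and two years. Under an assumed exponential 50% v 37.5% at five years, the planned difference is (1 − 0.5^0.2) − (1 − 0.625^0.2) ≈ 4 points at one year and about 7 at two.
- **That the looks rest on specific event counts.** Any count depends on an assumed recurrence rate.
- **That the 86% power is lost, or that a look near the close of recruitment is a mistake.** Unadjusted looks do not lower power, and stopping could still matter while patients are on three years of treatment and later follow-up.

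It is also fair to note that the 12–13% counts both directions. False claims of benefit are about half, 6.0–6.3%, against the usual 2.5% in that direction.

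**Conclusion.** The concern holds in conditional form. The article fixes a formal efficacy stopping rule on bare significance, without a stricter interim level or an adjusted final test, and leaves the level, the analysis set and the meaning of 10% undefined. Assuming two-sided 0.05 at every analysis and 1:1 allocation, overall error is about 12–13% if only the first 100 patients are analysed or if the 10% condition does not bind. It falls to roughly 7–11% (accrual of 100 per year) or 5–8% (233 per year) if all randomised patients are analysed with an absolute 10-point condition. The near-harmless end of that range needs accrual well above that observed. The rule should be corrected before it is used: followed literally at 0.05 it can produce a wrong conclusion, and the remedy is cheap.

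**What to change.** Replace the stopping sentence with a boundary on the log-rank test of the primary endpoint. Either p<0.001 at each interim look or O'Brien–Fleming-type alpha spending would serve. State the overall two-sided alpha and the final level: about 0.048 to hold 5% with the p<0.001 rule, or 0.05 accepting about 5.2%. Apply the test to all patients randomised by the date of the look. Either drop the 10% condition, or define it as absolute or relative at a named time point. Timing the looks by number of recurrences is optional.

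The cost is one paragraph in the protocol and the monitoring-board charter, with almost no change to the final critical value. The downside is a lower chance of an early efficacy stop.
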